**Proposed Methodology:**

Proposed Methodology: Study Design: This study will be a randomized, controlled clinical trial designed to evaluate the efficacy of cryotherapy in the recovery of delayed onset muscle soreness (DOMS) in CrossFit athletes after completing the Murph workout. Study Location and Population: The study will be conducted at the Capixaba training center, with support from the Laboratory of Neuroscience, Neuromodulation and Pain Study (LANNED), located in Alfenas, Minas Gerais. The study population will consist of 30 athletes who participate in training at the Capixaba box. Sample: Thirty athletes who participated in the Murph training at the Capixaba box will be selected. Participants will be recruited through invitations made directly at the Capixaba box, where the athletes usually train regularly. Brief presentations will be given before or after the training sessions to explain the objectives and importance of the study, as well as the inclusion and exclusion criteria. In addition, informational pamphlets will be distributed and posters will be posted around the box, containing details about the study and contact information for the researchers. Individuals will be divided into 2 groups: the control group and the intervention group, allocated through a randomization process performed using the Research Randomizer website. Sample Randomization: Volunteers will be divided into CG and IG through randomization, using the Research Randomizer website to ensure random allocation of participants. Sample Calculation: The sample calculation will be performed according to Cariappa (2006), estimating 15 volunteers per group to ensure a statistical power of 85% (ß=0.20) and a significance level of p<0.05. Assessment Instruments: Several instruments will be used to assess the pain and recovery of participants: 1.

Assessment Questionnaire for Application of the Protocol: Collects information on supplementation, diet, training frequency, use of therapeutic modalities and sleep quality. 2. Visual Analog Scale (VAS): Assesses pain intensity, graded from 0 to 10. 3. BORG: Assesses the perception of physical effort, using a scale from 0 to 10. 4. Brief Pain Inventory Scale (BPI): Assesses pain intensity and its impact on daily activities. 5. Questionnaire for the Assessment of Musculoskeletal Pain in Exercise Practitioners (Q-ADOM): Identifies the characteristics of pain and its influence on the practice of physical exercise. 6. Algometer: Measures sensitivity to pain by applying controlled pressure. 7. Thermographic Camera: Detects infrared radiation emitted by the body, visualizing the temperature of the skin surface. 8. CK Protein Quantification: Measurement of creatine kinase (CK) levels in blood as a marker of muscle damage. Intervention: The intervention will consist of cold water immersion sessions (cryotherapy) immediately following the Murph workout. The water temperature will be kept below 15°C and the duration of the immersion will be 10 minutes. The cryotherapy session will involve immersing the athletes' legs in a suitable container, ensuring that all major muscle areas involved in the exercise are treated. Experimental Procedures: Initially, baseline data will be collected using E-ADOM, BPI, VAS, algometry, thermography and blood samples to measure CK. After baseline data collection, athletes will perform the Murph WOD. After the workout, the cryotherapy intervention will be performed. Data will be collected again 24, 48 and 72 hours post-workout to assess the effects of the intervention on DOMS.

**Inclusion Criteria:**

Participants must be between 18 and 45 years of age and have at least 6 months of regular CrossFit training experience, training at least three times per week. It is essential that athletes be considered healthy and have no current or chronic musculoskeletal injuries that could interfere with the performance of the Murph WOD or the application of cryotherapy. Additionally, participants must not have performed the "Murph" WOD or similar intensity exercises in the four weeks prior to the start of the study.

All participants must provide written informed consent indicating that they understand the study procedures, risks, and benefits. They must also be available for training sessions, cryotherapy application, and subsequent assessments within the time frame established by the study. Athletes' body mass index (BMI) must be between 18.5 and 30 kg/m² to exclude extremes of body mass that could influence the results. Additionally, participants must not have used cryotherapy regularly as a recovery method in the three months prior to the study. It is important that athletes demonstrate the ability to follow study instructions and protocols consistently and correctly. Finally, participants must be able to read and understand the language in which the study and informed consent are presented, ensuring that they understand all study instructions and requirements.

**Exclusion Criteria:**

Participants will be excluded if they have any medical condition that could be exacerbated by intense exercise or cold exposure, such as severe cardiovascular, respiratory or metabolic disease. Athletes with a history of chronic or recent musculoskeletal injuries that could interfere with the performance of the Murph WOD or the application of cryotherapy will also be excluded.

In addition, individuals who have performed the WOD Murph or similar intensity exercises in the four weeks prior to the start of the study will be excluded to avoid effects of previous training. Participants who have used cryotherapy regularly as a recovery method in the three months prior to the study will also not be included to ensure that the intervention is novel to all subjects and its effects can be more clearly assessed.

Athletes who are unable to provide written informed consent or who do not fully understand the study procedures, risks and benefits will be excluded. Likewise, individuals who are not available to participate in all training sessions, cryotherapy application and subsequent assessments within the established study period will be disregarded. Those who present a body mass index (BMI) outside the range of 18.5 to 30 kg/m², to exclude extremes of body mass that could influence the results, will also be excluded.

Participants who do not demonstrate the ability to follow study instructions and protocols consistently and correctly will be excluded to ensure uniformity in the application of recovery methods. Individuals who cannot read and understand the language in which the study and informed consent are presented will be excluded, ensuring that all participants fully understand the instructions and requirements of the study. In addition, athletes who are using specific dietary supplements for muscle recovery or anti-inflammatories will be excluded, as these substances may interfere with the results of the research.

Risks:

Cryotherapy, although widely used and generally safe, may present some potential risks. Exposure to extremely low temperatures may cause temporary discomfort, including a sensation of intense cold, tingling, or numbness of the skin. In rare cases, immersion in cold water may result in skin injuries such as frostbite or frostbite if the temperature is not properly monitored. Individuals with pre-existing medical conditions, such as cardiovascular, respiratory, or metabolic problems, may be at greater risk of adverse complications due to vasoconstriction and systemic response to cold. Therefore, prior medical evaluation will be performed to identify and exclude such individuals.

Participants may also experience a temporary increase in muscle stiffness or discomfort after cold water immersion, especially if they are not accustomed to this type of therapy. Additionally, blood collection to measure creatine kinase (CK) levels may cause mild discomfort, bruising, or infection at the venipuncture site, although these risks are minimal when proper aseptic procedures are followed.

Benefits:

The benefits of participating in the study include the potential for reduced DOMS and improved muscle recovery, allowing athletes to return to their physical activities more quickly and with less discomfort. Participants will have access to a potentially effective therapeutic intervention that may not be available to them outside of the study context. Additionally, the data obtained may provide valuable insights into the efficacy of cryotherapy, contributing to the development of more effective recovery practices in the field of CrossFit and sports in general.

Participants can also benefit from more detailed monitoring of their fitness and response to exercise, with feedback and guidance from qualified professionals. This monitoring can help them better understand how their body responds to intense training and recovery strategies, potentially improving their exercise performance and preventing future injuries.

In terms of scientific contribution, the results of the study can benefit the wider sports community by providing evidence that can guide the implementation of effective recovery strategies for other athletes. As a risk-minimizing measure, all participants will first undergo a pre-medical evaluation to identify possible contraindications for cryotherapy. This evaluation will include a detailed physical examination and a review of medical history to exclude individuals with cardiovascular, respiratory or metabolic conditions that may be exacerbated by cold exposure.

During cryotherapy sessions, the water temperature will be strictly monitored and kept below 15°C, using calibrated thermometers to ensure accuracy. Immersion will be limited to a maximum of 10 minutes to avoid any damage to the skin or underlying tissues. Furthermore, supervision by qualified professionals throughout the intervention will ensure that any discomfort or adverse effects are immediately identified and treated. Participants will be instructed to report any abnormal sensations or discomforts during the immersion, allowing immediate interruption of the session if necessary.

To minimize the risks associated with blood collection for measurement of creatine kinase (CK) levels, strict aseptic procedures will be followed. Collection will be performed by trained professionals using sterile materials to reduce the risk of infection. In addition, puncture sites will be carefully selected and monitored to prevent bruising and other minor complications.

Participants will receive detailed instructions on study procedures and safety measures before the intervention begins. These instructions include guidance on the importance of proper hydration, warming up and cooling down before and after workouts and the cryotherapy session. Information will also be provided on how to monitor and report any adverse effects following the sessions. In addition to immediate safety measures, a continuous monitoring system will be established to monitor participants throughout the study. This will include regular assessments of muscle pain and other symptoms using standardized methods such as the Visual Analogue Scale (VAS), the Brief Pain Inventory (BPI) and the Questionnaire for Assessment of Musculoskeletal Pain in Exercisers (Q-ADOM). The use of algometers and thermal imaging cameras will provide objective assessments of pain and inflammation, ensuring that any significant changes in participants' condition are detected early.

In the event of any adverse event or complication, participants will have immediate access to appropriate medical care. Emergency protocols will be established and professionals involved in the study will be prepared to deal with any unexpected situation.

**Data Analysis Methodology:** Initially, descriptive analyses will be performed to summarize the demographic and clinical characteristics of the participants, as well as the results of the pain measurements. To compare pain levels before and after the cryotherapy intervention, paired t-tests or repeated measures analysis of variance (ANOVA) will be used, depending on the normality of the data. If the data do not follow a normal distribution, nonparametric tests such as the Wilcoxon test will be applied.

Additionally, multiple regression analyses may be performed to identify potential factors that influence the efficacy of cryotherapy, such as age, gender, CrossFit experience, and training intensity level. Correlation analyses will be conducted to investigate the relationships between different pain assessment methods and CK levels. Statistical significance will be set at a level of  $p < 0.05$ . All data will be analyzed using SPSS 20 statistical software.

Primary Outcome:

This research is expected to contribute to more accurate protocols and assessment methods for DOMS. It will provide coaches, physiotherapists, and athletes with concrete data on how to optimize post-exercise recovery, improving performance and adherence to training programs. It will also fill a significant gap in the literature regarding the effectiveness of post-exercise recovery strategies.

Sample Size in 30  
Date of First Recruitment: 08/11/2024

| Recruitment Countries          |         |                            |
|--------------------------------|---------|----------------------------|
| Country of Origin of the Study | Country | No. of survey participants |
| Yes                            | BRAZIL  | 30                         |

Other Information

Will there be use of secondary data sources (medical records, demographic data, etc.)?  
No

Report the number of individuals approached personally, recruited, or who will undergo some type of intervention at this center search:  
30

Groups into which research participants will be divided at this center

| Group ID    | No. of Individuals | Interventions to be carried out |
|-------------|--------------------|---------------------------------|
| Control     | 15                 | They will not do cryotherapy    |
| Cryotherapy | 15                 | Cryotherapy                     |

Is the Study Multicenter in Brazil?  
No

Do you propose waiving the TCLE?  
No

Will samples be retained for bank storage?  
Yes

Justification:  
Yes, samples will be retained for bank storage. Blood samples collected to measure creatine kinase (CK) levels will be stored in a biological sample bank. This storage will allow for future additional analyses that may arise as relevant to the study or to subsequent research related to delayed onset muscle soreness (DOMS) and muscle recovery. Samples will be collected following strict handling and conservation protocols, ensuring the integrity and viability of the samples for future analyses. All samples will be coded to ensure participant confidentiality and privacy, and stored under controlled conditions. temperature and safety at the Laboratory of Neuroscience, Neuromodulation and Pain Study (LANNED). Participants will be informed about the retention and storage of samples during the informed consent process, ensuring that they are aware of and in agreement with the use prolonged storage of your biological samples for research purposes.

Execution Schedule

| Stage Identification         | Start (DD/MM/YYYY) | End Date (DD/MM/YYYY) |
|------------------------------|--------------------|-----------------------|
| Data analysis                | 11/01/2024         | 04/30/2025            |
| Article writing              | 04/30/2025         | 06/30/2025            |
| Project submission           | 08/27/2024         | 08/27/2024            |
| Project writing              | 06/28/2024         | 06/28/2024            |
| Protocol execution           | 11/01/2024         | 11/15/2024            |
| Training in the use of tools | 10/01/2024         | 10/31/2024            |

Financial Budget

| Budget Identification | Type    | Value in Reais (R\$) |
|-----------------------|---------|----------------------|
| Crushed ice           | Costing | R\$ 200.00           |
| Elisa kit             | Costing | R\$ 1,500.00         |
| Total in R\$          |         | R\$ 1,700.00         |

Other information, justifications or considerations at the researcher's discretion:  
Correction of Pending Issues: 1. Clarify regarding the collection of biological material (blood) - location of collection and disposal of biological materials. A: The following text was included in item 5.8.8: The collection of biological material, specifically blood samples, will be carried out in an appropriate environment within the training center, where all biosafety standards will be strictly followed. The procedure will be carried out by a qualified and experienced nurse, ensuring that the collection is done in a safe and hygienic manner. The collected material will be used exclusively for the analysis of creatine kinase (CK) levels and other possible biomarkers related to the study. After the collection, the blood will be stored in specific tubes and kept under controlled conditions until analysis. Biological materials and all items used during collection, such as needles, syringes, and other disposable equipment, will be properly discarded in containers suitable for biological waste, in accordance with current regulations on the disposal of hospital waste. 2. Enter all researchers in all documents (TCLE and detailed project). A: The inclusions were made. 3. Clarify in the TCLE that the participant, after randomization, you may be allocated to a group that will undergo cryotherapy or a group that will not undergo this intervention. In the TCLE presented apparently all volunteers will undergo cryotherapy. A: It was included in item 1 of the TCLE and in item 5.8.9 of the project detailed. 4. Clarify the need for two TCLEs for this research, considering that they were attached to the Plataforma Brasil two versions of the TCLE (TCLE\_GELO.docx files), the first submitted on 06/28/24 and the other on 07/08/2024. A: A inclusion corrected on 07/08/2024, not excluding the version of 06/28/2024. However, in the present submission, these two

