For a more objective assessment, we will use algometry, which measures pain sensitivity by applying controlled pressure to the gastrocnemius muscle. In addition, we will use thermographic imaging to observe the temperature of the gastrocnemius muscle, which may indicate inflammation or other physiological processes. Finally, we will collect blood samples to measure levels of creatine kinase (CK), an enzyme that serves as a marker of muscle damage. Analyzing these levels will provide us with important information about the degree of muscle damage caused by training.

After collecting baseline data, athletes will perform the WOD Murph, which consists of running 1 mile, performing 100 pull-ups, 200 push-ups, 300 air squats, and running another 1 mile, an intense physical activity that generates a DOMS.

After completing the training, we will perform an intervention with immersion cryotherapy. An ice bath will be provided, in which the athlete will enter covering the entire gastrocnemius muscle. The application of ice to the participants' muscles aims to reduce inflammation and pain, promoting faster recovery.

To evaluate the effects of the cryotherapy intervention, we will repeat the collection of all data collected pre-workout at 24, 48 and 72 hours after training for possible conclusions.

Financial Support

| CNPJ | Name | E-mail | Telephone | Type             |
|------|------|--------|-----------|------------------|
|      |      |        |           | Financing
Own |

Keyword

| Keyword                          |
|----------------------------------|
| high intensity interval training |
| delayed onset muscle soreness    |
| cryotherapy                      |

Study Details

Summary:

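### The stated pain tests use the collected baseline only as the before level, never as a covariate, and name no arm term; a baseline-adjusted between-arm model would usually be more precise at 15 per group

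*Protocol*

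**What the plan says.** **Measurements.** Under Proposed Methodology (Experimental Procedures) the protocol states that "baseline data will be collected using E-ADOM, BPI, VAS, algometry, thermography and blood samples to measure CK". Under Design it adds that "we will repeat the collection of all data collected pre-workout at 24, 48 and 72 hours after training". These measures cover everything named in the secondary objectives: algometry, VAS, BPI, Q-ADOM (E-ADOM in places), CK and thermography. The Borg effort scale is listed as an instrument, but it is not in the baseline list and not in the objectives.

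**Analysis.** Data Analysis Methodology sets out to compare pain levels before and after cryotherapy, and says that "paired t-tests or repeated measures analysis of variance (ANOVA) will be used, depending on the normality of the data". Non-normal data go to nonparametric tests such as the Wilcoxon. An optional multiple regression looks for factors that influence efficacy and gives age, gender, CrossFit experience and training intensity as examples. CK appears in that section only in correlations with the pain measures. Thermography does not appear there.

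**Sample size.** The Sample Calculation text reads "estimating 15 volunteers per group" and continues "to ensure a statistical power of 85% (ß=0.20) and a significance level of p<0.05". It gives no effect size, SD or baseline-to-follow-up correlation.

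**The concern.** The Hypothesis section compares athletes who receive cryotherapy with athletes who do not. A paired test looks at change within athletes, and no arm factor is named for the repeated-measures ANOVA. If arm were simply added to that sentence, the baseline would still be handled as an outcome level or subtracted as part of a change score. Both carry its full noise into the treatment comparison.

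With 15 per group and no stratification described, chance imbalance at baseline is likely. The standard error of a baseline difference is sqrt(2/15) = 0.365 SD. A difference above 0.25 SD therefore arises in about 49% of randomisations, and one above 0.5 SD in about 17%. A between-arm change score is still unbiased over randomisations, but with equal SDs it over-corrects such an imbalance. ANCOVA estimates how much correction the data support. At this sample size the difference in precision can be worth several athletes per arm.

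**Working it through.** **Inputs from the protocol:** 15 per group, significance level 0.05 (sidedness not stated).

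**Assumptions:** two-sided test; correlation rho between baseline and follow-up; ratio k of baseline SD to follow-up SD. The protocol gives neither rho nor k.

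**1. The plan's own figure.** The 15 per group cannot be reproduced, because there is no effect size and because 85% power and a beta of 0.20 contradict each other. Solved backwards with a two-sample t-test (28 df), 15 per group detects 1.06 SD at 80% power and 1.13 SD at 85%. I use d = 1.134 as an anchor only.

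**2. Variance of the between-arm contrast**, in units of the follow-up variance:
- Change score: 1 + k² − 2·rho·k, which is 2(1 − rho) when k = 1.
- ANCOVA: (1 − rho²) × (1 + 1/26). The second factor is the approximate cost of estimating the slope at this sample size.

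Power is the upper tail of a noncentral t beyond its 0.975 critical value. The noncentrality is d·sqrt(15/2)/sqrt(variance), with 28 df for change and 27 df for ANCOVA.

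Example at rho = 0.5, k = 1. Change: variance 1.00, noncentrality 1.134 × 2.739 = 3.10, power 85.0%. ANCOVA: variance 0.75 × 1.0385 = 0.779, noncentrality 3.10/0.883 = 3.52, power 92.4%.

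| rho (k = 1) | Variance, change | Variance, ANCOVA before slope cost | Power, change | Power, ANCOVA with slope cost |
|---|---|---|---|---|
| 0.3 | 1.40 | 0.91 | 71.7% | 86.8% |
| 0.5 | 1.00 | 0.75 | 85.0% | 92.4% |
| 0.7 | 0.60 | 0.51 | 97.2% | 98.4% |

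Before the slope cost, a change-score analysis would need 15 × 1.40/0.91 = 23, 15 × 1.00/0.75 = 20 and 15 × 0.60/0.51 = 18 per group to match ANCOVA at 15.

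**3. Where the gain disappears.** With k = 0.3 and rho = 0.3, the change variance is 1 + 0.09 − 0.18 = 0.91, the same as ANCOVA before the slope cost. Power is then 88.1% for change and 86.8% for ANCOVA. At rho = 0.1, ANCOVA (83.9%) is also slightly below an unadjusted comparison of follow-up values (85.0%).

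**4. All three follow-up visits.** Assume equal correlation 0.5 between all visits, k = 1 and d = 0.8 at each follow-up.
- Group-by-time F test over four visits: the arm differences 0, 0.8, 0.8, 0.8 deviate from their mean 0.6 with sum of squares 0.48. Noncentrality is 7.5 × 0.48/0.5 = 7.2 on 3 and 84 df. Power is about 58% (59% in one simulation of 4,000 runs).
- Change score on the three-visit mean: variance 2/3, squared noncentrality 7.5 × 0.64/0.667 = 7.2 on 1 df. Power is about 73% to 74%.
- ANCOVA on the three-visit mean: variance (2/3 − 0.25) × 1.0385 = 0.433, squared noncentrality 4.8/0.433 = 11.1. Power is about 89%.

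The first two tests have the same noncentrality, so the step from 58% to about 73% comes only from replacing a 3-df test by a 1-df contrast. The covariate accounts for the step from about 73% to 89%.

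**The case against.** - **The sentence governs pain levels only.** This stands. A reader might infer that the protocol also treats the CK and temperature baselines as a before level. It does not say so: neither measure has a stated comparison test. The quoted sentence thus reaches algometry and the pain scales, and the fix has to supply an analysis for CK and thermography.
- **The comparators are hypothetical.** This also stands. The protocol states neither a between-arm change score nor a group-by-time test. The power figures show what baseline adjustment adds once an arm comparison is written in. They do not measure a loss from an analysis that the protocol specifies. The missing arm term is the more serious fault in the sentence, and one rewrite cures both.
- **This is a preference that a statistical analysis plan may settle.** Partly right. A between-arm change score is valid in a randomised trial, the regression list is open-ended, and an unseen plan could add ANCOVA. But the protocol names its tests, and a plan that follows them inherits the weakness.
- **The gain may be trivial or negative.** Right for some measures. Healthy, uninjured athletes may start near the floor on VAS and BPI, which leaves little baseline spread to use.

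**Conclusion.** The point holds as a recommended improvement, not as an error that biases the result. The protocol collects a baseline for every measure in its objectives, uses it for pain only as the before level, makes it a covariate nowhere and names no arm term.

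Under equal SDs and d = 1.13, adjustment adds about 15 points of power at rho 0.3, 7 at rho 0.5 and 1 at rho 0.7. The three-visit mean (d = 0.8, rho 0.5) gains about 16 points. All of this rests on assumed values of rho and the SD ratio. The benefit should be expected mainly for algometry, CK and thermography, and may be nil or minus 1 to 2 points for VAS and BPI.

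Three stronger readings are not supported:
- That baseline adjustment lifts power from 59% to 90%. About half of that gap is the change from a 3-df test to a 1-df contrast.
- That ANCOVA has the smaller variance at every correlation between 0 and 1. At 15 per group this fails when rho is low or baseline spread is small.
- That the stated 85% power is forfeited. That figure has no effect size behind it and contradicts its own beta.

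**What to change.** Replace the paired-test and repeated-measures sentence in Data Analysis Methodology. For each outcome in the objectives, including CK and thermography, compare cryotherapy with control in one of two ways:
- by ANCOVA on the post-workout value, or
- by a mixed model of the 24, 48 and 72 hour values.

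Either model should contain arm and the athlete's own baseline value as a covariate. Log-transform CK at both baseline and follow-up. Report the adjusted between-arm difference with its 95% confidence interval.

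The change is wording only. It needs no extra athletes, visits or samples, and SPSS 20, the software named, can fit both models. The statistical cost is one degree of freedom for the covariate, with the possible loss of 1 to 2 power points where the baseline carries little information. The same rewrite supplies the between-arm comparison that the Hypothesis section requires.
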